#### Caregiver recruitment and screening

Caregivers of children visiting the practice will be informed about the study using multiple methods (e.g., posters, brochures, PCP referral). Recruitment materials, available in English and Spanish, direct caregivers to their PCP and a website with more information and a short orientation video. Caregivers complete an online screening process. Eligible caregivers will then be given login credentials to access and complete an online consent and the baseline assessment via a smartphone, tablet, or computer. Caregivers who cannot read or write and caregivers without a smartphone or computer are directed to call the study coordinator to complete the screening and consent process.

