##### Primary care providers (PCPs)

We seek to enroll all eligible PCPs at participating practices (*M* = 4.4 PCPs per practice, range: 1–10) to maximize the likelihood that families have an enrolled PCP and enhance generalizability. All PCPs will be provided access to training and encouraged to deliver DOCC. PCPs in practices randomized to TEAM will participate in Team Facilitation.

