#### Caregivers

We will enroll up to 25 caregivers of 5–12-year-old children in each practice for a possible total of 600 caregivers. Eligibility criteria are (1) child age (5–12 years), (2) parent/guardian with parental rights, and (3) child meets clinical cutoff on 7-item externalizing problems scale of the Pediatric Symptom Checklist-17 (PSC-17) [117]. Based on prior trials, we expect to recruit more female than male caregivers and for participants to vary in race/ethnicity by practice. Our primary informant is the caregiver due to the children’s young age and ethical concerns about assessing children without face-to-face contact.

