#### Care team facilitation (TEAM)

TEAM is a phased approach designed to improve providers’ skill in using DOCC, teamwork quality, and team effectiveness. The TEAM facilitator is a licensed clinician who delivered DOCC in a prior trial and has lived experience as a consumer of integrated care for a child with ADHD. TEAM facilitation will occur via a graded schedule of videoconference calls over 18 months (weekly to bimonthly).

In the first phase of TEAM, the facilitator will engage the care team in identifying barriers and facilitators, enhancing motivation to use DOCC, and setting goals for implementation in their practice. The second phase focuses on reviewing and revising roles, responsibilities, and workflows within the team to improve collaboration, coordination, and use of DOCC. As part of this phase, the facilitator will support the team in developing effective communication and problem-solving skills. The third phase focuses on increasing the team’s competency and fidelity to DOCC through ongoing training in treatment content (e.g., didactics, modeling, role plays), structured reviews of patient progress, audit and feedback on use of the patient registry, consultation on challenging cases, and support in overcoming barriers and balancing model adaptations and fidelity. The last phase of TEAM focuses on the team’s capacity to sustain and continually improve DOCC in their practice. The facilitator will conduct structured team debriefings and encourage the team to identify and address potential problems in team processes. The facilitator will also guide the team in reflecting on implementation, reviewing and revising implementation goals, and planning for sustainability and continuous quality improvement.

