### Procedures

#### Randomization

For feasibility, the trial will occur in three cohorts. Randomization will occur at the beginning of each planned cohort. If possible, we will stratify the practices in each cohort by Medicaid rate before randomizing. Randomization will be conducted by the project’s data manager using random number generation in SAS. Practices will be informed of randomization after baseline data collection is completed. Research staff who have contact with participants will be unaware of implementation condition.

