### Statistical analyses

#### Aim 1

Our primary analytical tool for Aim 1 will be a two-way analysis of variance with interaction using mixed-effects linear models for continuous outcomes and generalized linear mixed models for categorical variables. We will use an intent-to-treat approach. We will examine patterns of missingness and, if necessary, use imputation methods using available covariates [141, 142]. For exploratory analyses, we will use variable selection methods such as Lasso and elastic net to get parsimonious models that fit well. Analyses will be conducted at the end of the trial; no interim analyses are planned.

For implementation outcomes, we hypothesize that relative to REP only, TEAM, LEAD, and their interaction will significantly improve (1) the number of DOCC service encounters per case and (2) collaborative care competencies within the practice. We will test effects on outcomes at months 6, 12, 18, and 24. Fixed effects include time, condition, and practice, and random effects will account for nesting. We will conduct planned contrasts to test differences between conditions.

For patient outcomes, we hypothesize that relative to REP only, TEAM, LEAD, and their interaction will significantly improve (1) child symptom severity and (2) quality of life. Fixed effects include time and condition, and random effects will account for nesting. As exploratory analyses, we will run larger models adjusting for demographic and baseline clinical variables and assess goodness of fit.

#### Aim 2

We hypothesize that TEAM practices will show significant gains in our proposed TEAM targets (team functioning, integration/quality) and that LEAD practices will show significant gains in our proposed LEAD targets (implementation leadership, implementation climate). We will use larger models to adjust for demographic and baseline clinical variables, test goodness of fit, and compare different time periods to check model fit. We will test if the association between each condition (TEAM, LEAD) and each implementation outcome is mediated by their respective targets and explore serial mediation.

#### Aim 3

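### Children can be recruited by PCPs who know their practice's condition, and the primary model for encounters per enrolled child has no child-level baseline covariate

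*Protocol article*

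**What the plan says.** Under Randomization, practices are randomized at the start of each of three cohorts, and "Practices will be informed of randomization after baseline data collection is completed". The masking statement there covers the research team: "Research staff who have contact with participants will be unaware of implementation condition". The audio rater is also masked (Fidelity to DOCC). PCPs and care managers are not described as masked, and under Primary care providers "PCPs in practices randomized to TEAM will participate in Team Facilitation".

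Under Caregiver recruitment and screening, families are "informed about the study using multiple methods (e.g., posters, brochures, PCP referral", and the recruitment materials "direct caregivers to their PCP and a website with more information". Screening is then done online by the caregiver, or by telephone with the study coordinator. Under Caregivers, "We will enroll up to 25 caregivers" in each practice, and the child must reach the PSC-17 externalizing cutoff.

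The primary outcome (Services Provided Log) is the count of DOCC encounters for each patient. For implementation outcomes, Statistical analyses, Aim 1 lists time, condition and practice as fixed effects, plus random effects for nesting. Baseline adjustment comes in the next paragraph, on patient outcomes: "As exploratory analyses, we will run larger models adjusting for demographic and baseline clinical variables and assess goodness of fit". Aim 2 also mentions larger models adjusted for demographic and baseline clinical variables.

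**The concern.** In a cluster trial, randomizing practices balances practices in expectation. It does not balance children who are chosen after the practice knows its condition. Here a PCP who may know the condition is one route into the study. TEAM works on provider motivation and workflow, and LEAD works on leaders' attention to DOCC, so both could plausibly change which children are referred and how many. Enrolment is capped at 25 per practice but not fixed, so numbers can differ as well.

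Case mix can feed the primary outcome directly. The DOCC section leaves session frequency and dose to the care team to tailor to the child, so encounters should depend partly on need. A difference in encounters per case could then reflect who was enrolled and not how well DOCC was implemented. It could go either way: facilitated practices might bring in harder or less motivated families, or practices without facilitation might enrol only a few willing ones. Analysing practices as randomized does not cure this, because the analysed children are themselves selected after randomization.

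**Working it through.** **Step 1: timing, from the text.** The Randomization section does not say whose baseline must be complete before disclosure. Two readings are possible.

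- Staff baseline at month 0. Disclosure then comes early, and children recruited as they visit enrol afterwards.
- Caregiver baseline as well. The recruitment section does call the caregiver's first assessment a baseline. Disclosure would then wait until a practice had finished enrolling up to 25 children.

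The first reading fits the rest of the article better. Staff have their own month-0 assessment, "TEAM facilitation will occur via a graded schedule of videoconference calls over 18 months", and implementation outcomes are tested at months 6, 12, 18 and 24. It remains an inference. On neither reading does the article state that children are identified before disclosure or independently of PCPs who know the condition.

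**Step 2: the plan's own figure.** Power and sample size gives 80% power for an effect size of 0.42 on the number of sessions. Alpha, sidedness and the ICC for this outcome are not given, so the figure cannot be reproduced from stated inputs. Assume two-sided alpha 0.05 and 25 cases per practice. The detectable effect is then (1.960 + 0.842) × √(2 × DE / n), with DE = 1 + 24 × ICC:

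- 12 v 12 practices, n = 300 per side, ICC 0.10: DE = 3.40, giving 2.802 × √(6.80/300) = 0.422.
- 6 v 6 practices, n = 150 per side, ICC 0.03: DE = 1.72, giving 2.802 × √(3.44/150) = 0.424.

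So 0.42 is attainable under either assumption. Neither makes any allowance for recruitment bias, and the point does not rest on which is right.

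**Step 3: illustrative size of bias.** Bias in outcome SDs = (shift between arms in a baseline factor, in SD) × (correlation of that factor with encounters). Both inputs are assumptions. The standard error implied by the plan's figure is 0.42 / 2.802 = 0.150. The two-sided rejection rate with no true effect is P(Z > 1.960 − bias/0.150) + P(Z < −1.960 − bias/0.150).

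Example: 0.3 × 0.3 = 0.09 SD; 0.09 / 0.42 = 21%; 0.09 / 0.150 = 0.60; rejection rate 9.2%.

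| Shift (SD) | Correlation | Bias (SD) | Share of 0.42 | False-positive rate |
|---|---|---|---|---|
| 0.2 | 0.1 | 0.02 | 5% | 5.2% |
| 0.2 | 0.3 | 0.06 | 14% | 6.9% |
| 0.2 | 0.5 | 0.10 | 24% | 10.2% |
| 0.3 | 0.1 | 0.03 | 7% | 5.5% |
| 0.3 | 0.3 | 0.09 | 21% | 9.2% |
| 0.3 | 0.5 | 0.15 | 36% | 17.0% |
| 0.5 | 0.1 | 0.05 | 12% | 6.3% |
| 0.5 | 0.3 | 0.15 | 36% | 17.0% |
| 0.5 | 0.5 | 0.25 | 60% | 38.5% |

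The range runs from negligible to serious. A shift of zero is equally compatible with the text.

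**Step 4: what the stated model does about it.** Time, condition and practice carry no information on the individual child. Condition is constant within a practice, so a practice term cannot separate case mix from the effect of condition.

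**The case against.** The strongest objection is that the timing is not established. If disclosure waits for caregiver baselines too, PCPs would not know the condition when they refer. That is possible on the wording but would hold up disclosure until enrolment ended, which fits poorly with recruitment at routine visits. What stands is that the order is inferred, not stated.

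There are also real safeguards: a fixed PSC-17 cutoff, screening completed by the caregiver, posters, brochures and a website alongside PCP referral, and masked research staff. They narrow the scope for selection. But the cutoff sets only a floor on severity, and none of them stops a PCP from choosing whom to refer among eligible children.

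Covariate lists are often left to the SAP, and the fixed effects named need not be exhaustive. That is fair as a general rule. Here, however, the article names the terms of the primary model and labels baseline adjustment exploratory in the neighbouring paragraph, so what it does fix leans the wrong way. Enrolment numbers by condition may already be covered by the CONSORT flow diagrams in Supplemental File 2, which is not shown.

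A reader might also infer that child case mix is ignored everywhere outside the clinical models. It is not. Aim 2 mentions adjusted models, and child baseline ADHD severity is listed as a family-level moderator. Neither puts a child covariate into the primary comparison.

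**Conclusion.** The point holds as an unprotected risk to the primary comparison, not as a demonstrated bias. The article leaves recruitment open to PCPs who know the condition, uses an outcome averaged over the children so enrolled, and states a primary model with no child-level covariate.

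Two stronger conclusions are tempting, and the documents support neither. The first is that referring PCPs will already know their practice's condition; that is the likelier reading but is nowhere stated. The second is that the bias amounts to a substantial share of the 0.42 effect. The illustrative 0.02 to 0.25 SD (5% to 60% of 0.42) rests wholly on the assumed shifts of 0.2 to 0.5 SD and correlations of 0.1 to 0.5. The false-positive rates further assume two-sided alpha 0.05. Neither size nor direction can be determined from the article. The case for acting is that the remedy is almost free and part of the information cannot be reliably recovered later.

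**What to change.** - In the primary model for encounters, prespecify adjustment for the screening PSC-17 externalizing score, baseline VADPRS severity and child age. Keep the unadjusted model as a sensitivity analysis.
- Adjust the clinical models for the same variables wherever baseline is not already in the model.
- Record referral route at screening, and compare numbers enrolled and baseline case mix by condition.
- State whether caregivers are identified before or after practices learn their condition.

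Two other checks are less useful than they look. A practice total of encounters does not escape the problem, because encounters are logged per patient and the total still depends on how many children enrolled and which ones. An analysis of self-referred children conditions on another post-randomization variable, and the materials send caregivers to their PCP anyway, so the routes are not cleanly separable. Treat any such subset as descriptive only.

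The cost is SAP wording and one field in the screening form. The PSC-17 score and age are needed for eligibility, and the VADPRS is already scheduled at month 0. The article says no data had been collected, so the field could still be added at that stage. The model becomes slightly larger and should gain some precision if the covariates predict encounters. Adjustment will not remove unmeasured differences such as family motivation.

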#### Professional and caregiver assessments

Practice staff will complete assessments at 0, 6, 12, 18, and 24 months. Caregivers will complete assessments at 0, 3, 6, and 12 months and provide consent for their child’s teacher to complete rating scales at each timepoint. Measures are listed in Table 2. All assessments can be completed online, on paper, or by phone with research staff. Participants will be paid for each completed assessment. We estimate high retention rates for practice staff (> 90%) and caregivers (> 85%) based on our previous trials (91–92%) [107–109]. We will use strategies from prior trials (e.g., trained staff, on-time bonus payments) to support retention.

**Table 2 Tab2:** Primary assessment constructs, measures, sources, and timepoints by study aim

Construct	Measure	Source	Month					
			0	3	6	12	18	24
**Aim 1: implementation outcomes**								
Total # of DOCC sessions received	SPL	Provider notes	During services					
Care management competencies	MHPRI	All staff	x		x	x	x	x
(Acceptability, appropriateness, feasibility)	(AIM, IAM, FIM)	All staff	x		x	x	x	x
**Aim 1: clinical outcomes**								
Child symptom severity	VADPRS	Caregiver	x	x	x	x		
Child symptom severity	VADTRS	Teacher	x	x	x	x		
Child health-related quality of life	PEDS-QL	Caregiver	x	x	x	x		
**Aim 2: mediators**								
Care team functioning	PCTDS (TDM)	All staff	x		x	x	x	x
Care team integration/quality	PICS	Caregiver	x	x	x	x		
Implementation climate	ICS (ISM)	All staff	x		x	x	x	x
Implementation leadership	ILS (ISM)	All staff	x		x	x	x	x
**Aim 3: moderators and other variables**								
Practice characteristics (e.g., size, % Medicaid)	PINS	Manager	x					
Staff characteristics (e.g., training, education)	SIF	CM	x					
Child characteristics (e.g., gender, minority status)	FIF	Caregiver	x					
Attitudes about delivering behavioral health care	PBS	All staff	x		x	x	x	x

Secondary constructs/measures are indicated by parentheses

*SPL* Services Provided Log, *MHPRI* Mental Health Practice Readiness Inventory, *AIM* Acceptability of Intervention Measure, *IAM* Intervention Appropriateness Measure, *FIM* Feasibility of Intervention Measure, *VADPRS* Vanderbilt ADHD Diagnostic Parent Rating Scale, *VADTRS* Vanderbilt ADHD Diagnostic Teacher Rating Scale, *PEDS-QL* Pediatric Quality of Life, *PCTDS* Primary Care Team Dynamics Survey, *TDM* Team Development Measure, *PICS* Pediatric Integrated Care Survey, *ICS* Implementation Climate Scale, *ISM* Inner Setting Measures, *ILS* Implementation Leadership Scale, *PINS* Practice Information and Needs Survey, *SIF* Staff Information Form, *FIF* Family Information Form, *PBS* Physician Belief Scale

### Measures

#### Background information

At baseline, each practice manager will complete a Practice Information and Needs Survey (PINS) form, and professionals will complete a Staff Information Form (SIF). Caregivers will complete a Family Information Form (FIF) to provide background information, including any other treatment services [118].

#### Implementation outcomes

##### Services Provided Log (SPL)

After each service encounter, providers will record the type of contact (e.g., treatment session, collaborative care meeting), individuals present, intervention content, and plans for next contact [107, 108]. Our primary outcome is the number of DOCC service encounters delivered to each patient by all providers.

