#### Aim 1: test the effects of TEAM and LEAD on implementation outcomes and child clinical outcomes

Our implementation outcomes are DOCC service delivery, specifically the number of encounters for each case (primary), and change in practice-level care management competencies (exploratory) at 4 timepoints (6, 12, 18, and 24 months). We will also examine secondary clinical outcomes (change in severity of child symptoms). We hypothesize that augmenting REP with TEAM alone or LEAD alone is superior to Standard REP, and that TEAM + LEAD is superior to all other conditions because it targets both levels.

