## Methods

### Study design

We propose a hybrid type 3, cluster-randomized effectiveness–implementation trial in a 2 × 2 factorial design in 24 pediatric primary care practices across Pennsylvania. After all sites receive Standard REP, they will be randomized to one of four conditions: (1) Standard REP only (continued technical assistance), (2) TEAM, (3) LEAD, or (4) TEAM + LEAD. Figure 1 outlines the trial design. Care teams will deliver DOCC to 25 children with elevated behavioral problems and their caregivers. We will collect longitudinal data from practice staff and caregivers. SPIRIT, CONSORT, and TIDieR checklists [113–115] are in Supplemental File 1, and CONSORT flow diagrams are in Supplemental File 2. All procedures were approved by the University of Pittsburgh Institutional Review Board.

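### The per-case primary outcome has no value for a randomized practice that enrols no child, and no listed outcome counts how many children a practice treats

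*Protocol article*

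**What the plan says.** The primary outcome is per child wherever the protocol article defines it. The Services Provided Log section says "Our primary outcome is the number of DOCC service encounters delivered to each patient by all providers". Aim 1 gives "specifically the number of encounters for each case (primary", and the Aim 1 hypothesis under Statistical analyses names "1) the number of DOCC service encounters per case".

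On numbers, the Caregivers section says "We will enroll up to 25 caregivers of 5–12-year-old children in each practice for a possible total of 600 caregivers". That is a ceiling, and no minimum is given. The Study design section words it flatly: "Care teams will deliver DOCC to 25 children with elevated behavioral problems and their caregivers".

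On timing, the Randomization section says "Randomization will occur at the beginning of each planned cohort". Practices learn their condition once baseline data are in. Caregiver recruitment and screening describes recruitment of families visiting the practice by several routes, one of them referral by the PCP. Each caregiver's baseline assessment comes after individual screening and consent.

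On the analysis set, Statistical analyses says "We will use an intent-to-treat approach". The article does not say how a randomized practice with no cases enters the primary comparison.

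The other implementation outcomes in Table 2 and under Measures are staff-rated care management competencies (exploratory in Aim 1) and acceptability, appropriateness and feasibility. The dosage criterion under Fidelity to DOCC is again applied case by case.

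**The concern.** The practice is the randomized unit, and TEAM and LEAD are meant to raise a practice's uptake of DOCC. Whether children enter DOCC at all can be a result of the strategy. TEAM works on motivation and implementation goals, LEAD works on practice barriers, and enrolment follows randomization. The primary outcome conditions on that result. It asks how many encounters a child received once enrolled, and has no term for how many children were enrolled.

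A practice that takes on no DOCC patients is the plainest implementation failure, yet it has no value on this outcome. It leaves the comparison instead of lowering its condition's mean. A practice with a handful of cases stays in with reduced weight. No other listed outcome counts children treated or total delivery, so a strategy that works mainly by bringing practices and families in could show little or nothing.

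**Working it through.** **The plan's own figure.** Power and sample size gives 80% power for an effect size of 0.42 on the number of sessions, without the ICC, cases per practice, alpha or contrast for this outcome. As a check, borrow the ICC of 0.01 and 20% attrition stated there for patient outcomes (25 × 0.8 = 20 cases in each of 6 practices, n = 120 per condition) and assume two-sided alpha 0.05:

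- Design effect: 1 + 19 × 0.01 = 1.19.
- Detectable effect: (1.960 + 0.842) × √(2 × 1.19/120) = 0.395, or 0.415 using t with 20 df.

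So 0.42 is plausible for one condition against another if practices reach about 20 analysed cases. Read as a 12 v 12 main effect, it implies an ICC of about 0.08 to 0.10.

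**Weight of a small practice.** With a random practice effect, weight is proportional to n/(1 + (n − 1) × ICC). The ICC for this outcome is not given, so a range is shown. At ICC 0.10, 5 cases give 5/1.4 = 3.57 and 25 cases give 25/3.4 = 7.35, a ratio of 0.49.

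| Cases | ICC 0.05 | ICC 0.10 | ICC 0.20 |
|---|---|---|---|
| 0 | 0 | 0 | 0 |
| 1 | 0.09 | 0.14 | 0.23 |
| 5 | 0.37 | 0.49 | 0.64 |
| 25 | 1 | 1 | 1 |

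If half the practices at each level of a factor enrol 5 instead of 25, power for 0.42 as a main effect (t, 20 df) falls from 0.91 to 0.78 at ICC 0.05 and from 0.76 to 0.63 at ICC 0.10.

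**What the per-case mean cannot show (assumed counts, six practices per condition).**

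- *Missed effect.* Comparison: two practices enrol nobody and four enrol 25 at 7 encounters, so 4 × 25 × 7/6 = 116.7 encounters per randomized practice. Facilitated: all six enrol 25 at 7, so 175. The per-case difference is 7 − 7 = 0.
- *Understated effect.* Same comparison condition; facilitated: all six enrol 25 at 8, so 200. The per-case mean rises from 7 to 8 (14%), while delivery per practice rises from 116.7 to 200 (71%).

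**When the sign could reverse.** If n children receive a encounters each and the strategy adds k more at b each, leaving the first n unchanged, the mean becomes (na + kb)/(n + k). This is below a only if b < a. For example, 5 children at 8 (total 40) against the same 5 at 8 plus 20 at 5 (total 140) gives means of 8.0 and 140/25 = 5.6. The documents give no information on b relative to a.

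**Precision of a practice-level outcome.** With one value per practice, the detectable difference at 80% power (t, 20 df) is about (2.086 + 0.860) × √(2/12) = 1.20 between-practice SDs for 12 v 12, and about 1.70 for 6 v 6.

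**The case against.** Several points on the other side are sound.

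- *Per-case counting is a legitimate choice.* It separates delivery from research recruitment, which also runs through posters, a website and online consent, and it matches the per-case dosage definition. A practice total mixes delivery with practice size (1 to 10 PCPs) and is cut off at the study's own cap. This is why the per-case primary outcome should stay.
- *Empty practices may be rare.* Sites were chosen as interested and are described as motivated. The documents give no enrolment distribution either way.
- *Handling of small or empty clusters can be left to the SAP,* which is not shown. That covers the analysis rule. It does not cover the choice of outcome and unit, which the article fixes itself.

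A reader might infer three stronger things that the documents do not support.

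- *That a strategy reaching more children will look harmful.* This needs added children to receive fewer encounters each, for instance because care-manager time runs out. One care manager is enrolled per practice, but works with PCPs and the care team. All PCPs are encouraged to deliver DOCC, and encounters by every provider count. Even 25 cases at an assumed 8 to 11 encounters make 200 to 275 in all, or 2.6 to 3.5 a week over an assumed 78 weeks. Reversal is neither shown nor ruled out.
- *That a practice which enrols families but fails to treat them escapes the analysis.* Under intent-to-treat those children should count as 0. Only few or no enrolments cause the loss. Because the log is filled in after an encounter, the zero should be stated.
- *That the two statements about 25 children are a material contradiction.* The Study design line reads as a target and the Caregivers section gives the operative limit.

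**Conclusion.** The concern holds in a limited form. The primary outcome is defined only for enrolled children, and enrolment has no floor and can respond to the strategy. The per-case comparison is therefore not intent-to-treat over the 24 randomized practices and can miss or understate an effect on how much DOCC a practice delivers. No listed outcome would reveal this.

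The structural part follows from the text: a practice with no cases has weight zero. All other sizes above rest on assumed ICCs and counts. The argument that the strategy itself affects enrolment assumes that families are enrolled after practices learn their condition. Randomization at cohort start and recruitment at visits point that way, although the baseline that precedes disclosure is not specified as staff or caregiver. Even if enrolment came first, a practice with no cases would still drop out.

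**What to change.** 1. Keep encounters per enrolled case as the primary outcome, and state that an enrolled child with no logged encounter counts as 0.
2. Prespecify a supporting practice-level analysis from the same log over all 24 randomized practices, with 0 where nothing was delivered. The outcomes are the number of children receiving at least one DOCC encounter and total DOCC encounters in a fixed implementation period. The model has TEAM, LEAD and their interaction, with practice size considered as a covariate.
3. Report it with its confidence interval beside the primary result and discuss any discordance. Do not let its sign override the primary result. For example, assume a true 26% gain in encounters, no effect on enrolment and a practice-total coefficient of variation of 0.5 to 0.7. The chance that the total points the wrong way in a 12 v 12 comparison is then Φ(−0.26/(CV × √(2/12))), about 10% to 18%.
4. Align the Study design wording with "in each practice for a possible total of 600 caregivers" and the ceiling it belongs to in the Caregivers section.

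The cost is analysis-plan wording, since the log is already part of the planned data collection. The downside is low precision: there are only 24 values, with about 1.2 between-practice SDs detectable for a main effect. The outcome is also truncated by the 25-case cap and partly reflects research recruitment and practice size.
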